##### Prepulse inhibition of acoustic startle response

3.5.4.1

PPI is the behavioral phenomenon whereby the magnitude of the startle response is inhibited when a short, loud startling sound (the pulse) is preceded by a weaker sound that does not itself elicit a startle reflex (the prepulse). The PPI training session will last approximately 12 minutes, contain 44 trials, and will be administered to all children. We will use a pulse consisting of a 105 dB, 50 ms white noise burst. The prepulse will consist of a 50 ms white noise burst of varying amplitude that is always softer than the pulse, delivered at three different intensities: 10% (soft), 25% (medium), and 40% (high) of the pulse amplitude. For the soft and high prepulse intensities, a fixed interstimulus interval (ISI) of 120 ms will be used between the prepulse and the pulse. For the medium prepulse intensity, ISIs of 60, 120, and 240 ms will be used. The session will begin with 2 practice trials containing white noise bursts at various soft intensities to allow the participant to relax and settle into the movie. Subsequently, 7 blocks of 6 trials will be presented. Each block will consist of one pulse-only trial and five prepulse-pulse trials. The order of trials will be randomized and will differ between blocks. The intertrial interval will be randomly set between 4 and 14 seconds.

*Dependent variables*

Acoustic startle response (ASR) amplitude and variability: The normalized peak eyelid closure amplitude in response to the pulse-alone trials and its standard deviation.ASR latency to peak: The time from pulse onset to the peak of the eyeblink response.Prepulse-elicited response amplitude: The normalized peak eyelid closure amplitude in response to the prepulse-alone.Prepulse-elicited response latency: The time from prepulse onset to the peak of the eyeblink response it elicits.Prepulse-pulse response amplitude and variability: The normalized peak eyelid closure amplitude in response to the pulse when it is preceded by a prepulse, and its standard deviation.Percent PPI: The percentage inhibition of the ASR amplitude due to the prepulse, calculated as: % PPI = 100 - [(mean ASR amplitude on prepulse-pulse trials)/(mean ASR amplitude on pulse-alone trials) × 100].Prepulse excitation: A measure of hyper-responsiveness to the prepulse itself.Habituation: The change in normalized ASR amplitude to pulse-alone trials over the course of the entire session.

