##### Startle habituation

3.5.4.2

All children will complete a second neurobehavioral assessment session lasting approximately 12 minutes that contains 22 stimulus trials. The session will begin with two practice trials to allow participants to acclimate to the stimuli. The remaining 20 trials will consist of short-term habituation assessments. We will present six 50 ms, 105 dB white noise pulses, delivered in either a rhythmic or random interstimulus interval (ISI) pattern, as previously described (22).

*Dependent variables*

Short-term habituation: The change in the normalized amplitude of reflexive eyeblinks between the first white noise pulse and the average of the subsequent five pulses, calculated for both random and rhythmic stimulus patterns.Cumulative response: The cumulative sum of the normalized eyeblink amplitude across all trials for both random and rhythmic stimulus patterns.Anticipatory blinks: The amplitude of eyeblinks occurring immediately (< 100 ms) prior to the onset of the pulse.

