##### General sensorimotor behavior

3.5.4.3

During the PPI and SH sessions, the smartphone’s front-facing camera and microphone passively capture a broad range of behavioral data, extending beyond the specific eyeblink responses required for the primary neurometric tests. Ten specific behaviors previously identified as differing between autistic and NA children will be analyzed in this study (22).

*Dependent variables:*

Task engagement: The percentage of trials in which the participant is not detectable within the smartphone’s camera frame.Headphone interaction: The percentage of trials with observed touching or adjustment of the headphones.Non-syllabic vocalizations: The frequency (percentage of trials) and total duration of non-linguistic vocal sounds.Postural stability: The degree of anteroposterior postural sway.Head movement: The percentage of trials with observed head rotation.Orofacial movement: The frequency and duration of mouth openings.Oculomotor activity: The mean amplitude of horizontal pupil movement per session.Vestibulo-ocular reflex (VOR) function: The correlation between the direction of head turns and compensatory pupil movement.Initial baseline variability: The variation in baseline (pre-stimulus) eyelid position during the first five trials of a session.Baseline stability: The change in the variability of baseline eyelid position from the start to the end of the session.

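### Prepulse-elicited amplitude is defined on prepulse-alone trials that the session does not contain, and the cumulative response is an unscaled sum that falls with every lost trial

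*Protocol article*

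**What the plan says.** **PPI session (section 3.5.4.1).** The session is enumerated completely. "The PPI training session will last approximately 12 minutes, contain 44 trials, and will be administered to all children". "The session will begin with 2 practice trials containing white noise bursts at various soft intensities". "Subsequently, 7 blocks of 6 trials will be presented". "Each block will consist of one pulse-only trial and five prepulse-pulse trials". Soft and high prepulses use a 120 ms interval; the medium prepulse uses 60, 120 and 240 ms. Among the dependent variables, prepulse-elicited response amplitude is "The normalized peak eyelid closure amplitude in response to the prepulse-alone". Prepulse-elicited latency is timed from prepulse onset to the peak of the blink it evokes. Prepulse excitation is described as over-responsiveness to the prepulse, without a formula.

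**Startle habituation session (section 3.5.4.2).** After two practice trials, 20 trials are scored. The cumulative response is "The cumulative sum of the normalized eyeblink amplitude across all trials for both random and rhythmic stimulus patterns". No division by the number of contributing trials is stated.

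**Trial validity and visibility.** Section 3.5.4 takes outcomes from valid normalized trials, recorded at 60 frames per second. Section 3.5.4.3 says: "Ten specific behaviors previously identified as differing between autistic and NA children will be analyzed". The first of these ten, task engagement, is "The percentage of trials in which the participant is not detectable within" the camera frame.

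**The concern.** The prepulse outcome and the trial list stand in the same section and do not fit each other: no scored trial type delivers the quantity that is defined. Whoever scores the recordings must improvise. The natural substitute, reading the blink before the pulse takes over, gives a window whose length depends on the interval. A value from a 60 ms trial and one from a 240 ms trial are then not the same measurement.

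The cumulative response can be computed, but it is not comparable between children who have different numbers of valid trials. A lost trial contributes nothing to the sum, just as a trial without a startle would. Since the article itself treats visibility in the frame as a group characteristic, a group contrast in this sum can arise from missing trials alone.

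Objective 3 compares PPI and habituation profiles between groups. Objectives 4 and 5 carry sensorimotor measures into association and mediation analyses. A missing trial type cannot be supplied once the children have been tested.

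**Working it through.** **1. Trial count, reproducing the stated 44**

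- Practice: 2
- Pulse-only: 7 × 1 = 7
- Prepulse-pulse: 7 × 5 = 35
- Total: 2 + 7 + 35 = 44, as stated
- Left for prepulse-alone: 44 − 44 = 0

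The five prepulse-pulse trials per block match the five conditions (soft/120, high/120, medium/60, medium/120, medium/240 ms), so each condition has 7 trials per child. The practice trials do not fill the gap. They serve to settle the child, their intensities are only described as soft and varied, and two trials cannot cover three prepulse intensities.

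**2. Window before the pulse**

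Frames = interval ÷ (1000/60 ms). The article does not say whether the interval runs from prepulse onset or from prepulse offset. The prepulse lasts 50 ms, which is 3 frames, so both readings are shown.

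| Interval | Frames, onset to onset | Frames, offset to onset |
|---|---|---|
| 60 ms | 3.6 | 6.6 |
| 120 ms | 7.2 | 10.2 |
| 240 ms | 14.4 | 17.4 |

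Soft and high prepulses have only the 120 ms interval. The pulse blink itself starts with some delay after the pulse, which lengthens each window by an amount the article does not give.

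**3. Effect of trial loss on the cumulative response**

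If a child's mean amplitude per trial is m and a share v of the 20 trials is valid, the expected sum is 20 × v × m. With equal m in both groups, the ratio of sums is v1/v2. With a between-child coefficient of variation (CV) of the sum and 100 children per group (section 2.2.4):

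z = (v2 − v1) / √[CV² × (v1² + v2²) / 100]

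Rejection probability ≈ Φ(z − 1.96) + Φ(−z − 1.96), at the planned 0.05 level. The valid-trial rates and CVs are assumptions; the article gives none.

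| Valid trials | CV | Ratio of sums | z | False rejection |
|---|---|---|---|---|
| 90% v 95% | 0.5 | 0.95 | 0.05/0.0654 = 0.76 | about 12% |
| 80% v 95% | 0.8 | 0.84 | 0.15/0.0994 = 1.51 | about 33% |
| 80% v 95% | 0.5 | 0.84 | 0.15/0.0621 = 2.42 | 68% |
| 70% v 90% | 0.5 | 0.78 | 0.20/0.0570 = 3.51 | 94% |

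A simulation checked this (3,000 runs per scenario, 20 trials, 100 per group, Welch t-test, equal true amplitude, 10% loss in one group).

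| Loss in the other group | Sum, CV 0.8 to 0.3 | Mean per valid trial |
|---|---|---|
| 10% (equal) | 5–6% | 5–6% |
| 20% | 17–74% | about 5% |
| 30% | 57–100% | about 5% |
| 40% | 94–100% | about 5% |

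Unequal loss is what inflates the error, and dividing by the number of valid trials removes it.

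**The case against.** Several points on the other side are sound.

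- **Only one outcome names the prepulse alone.** Latency and excitation do not. The amplitude definition omits the word trials, so it could be read as the response to the prepulse before the pulse arrives. That reading rescues the outcome only if a scoring window is stated, and none is.
- **The article gives no blink latency.** A reader might infer that only the 7 medium trials at 240 ms are usable. The documents do not show this; they show only that the window differs between intervals and that 240 ms is the longest.
- **The direction of trial loss is not stated.** A reader might infer that the sum would make autistic children look blunted. Section 3.5.4.3 says the behaviours differ between groups, not which group leaves the frame more often.
- **Rescaling may exist elsewhere.** Filtering, normalization and the stimulus patterns are referred to a cited source, and section 3.6.2 plans mixed models with trials nested in sessions, partly to handle missing data. Neither is stated to apply to this sum, which is already one figure per child, so this answers the point only in part.
- **The reach is limited.** The sample size rests on malnutrition prevalence. At most 4 of the 21 listed neurobehavioural variables (8 + 3 + 10) are affected, in a study that calls its aims hypothesis-generating.

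These points bound the severity. They leave the missing trial type and the unscaled sum in place.

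**Conclusion.** The point holds for specific outcomes. Prepulse-elicited amplitude has no scored trial that fits its definition; this follows from the article's own count and needs no assumption. Prepulse latency and excitation can be read only in a window that varies fourfold in nominal interval (60 to 240 ms), so their values are not comparable across intervals. The cumulative response falls in proportion to lost trials with no change in startle, and biases the contrast towards a weaker response in whichever group loses more.

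The size of that bias depends on rates the article does not give. Over the assumed scenarios in the first table, false rejection runs from about 12% to 94%. The upper figures need gaps of 15 to 20 percentage points in valid trials and should not be read as expected values. With equal loss there is no inflation.

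A reader might go further and infer that the startle outcomes as a whole cannot be obtained. The documents do not support that: startle amplitude and latency, prepulse-pulse amplitude, percent PPI, within-session and short-term habituation, and anticipatory blinks are all obtainable from the stated trials. This should be fixed, but it does not undermine the main sensorimotor measures.

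**What to change.** **Prepulse outcomes, one of two options:**

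1. Define amplitude, latency and excitation as scored from prepulse onset in a stated window that ends before the pulse response. Say whether the interval runs from prepulse onset or offset. Analyse by interval, and keep only the intervals that pilot recordings show to be long enough; the medium 240 ms trials are the safest. Give excitation a formula. Cost: wording, and possibly fewer prepulse outcomes reported.
2. Add one prepulse-alone trial to each block. Cost: 7 trials at a mean spacing of 9 s (midpoint of 4 to 14 s), 7 × 9 = 63 s, so about one minute per child, plus a change to the stimulus sequence of a proprietary application. With one such trial per block, state which prepulse intensities it uses.

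**Cumulative response:** replace the sum with mean amplitude per valid trial, or analyse trial amplitudes directly in the mixed model already planned, for random and rhythmic patterns separately. Report the number of valid trials by group. Cost: an outcome definition and one descriptive table; no extra data.

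Both changes are best made at the pilot stage, before main data collection.

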##### Startle habituation

3.5.4.2

All children will complete a second neurobehavioral assessment session lasting approximately 12 minutes that contains 22 stimulus trials. The session will begin with two practice trials to allow participants to acclimate to the stimuli. The remaining 20 trials will consist of short-term habituation assessments. We will present six 50 ms, 105 dB white noise pulses, delivered in either a rhythmic or random interstimulus interval (ISI) pattern, as previously described (22).

*Dependent variables*

Short-term habituation: The change in the normalized amplitude of reflexive eyeblinks between the first white noise pulse and the average of the subsequent five pulses, calculated for both random and rhythmic stimulus patterns.Cumulative response: The cumulative sum of the normalized eyeblink amplitude across all trials for both random and rhythmic stimulus patterns.Anticipatory blinks: The amplitude of eyeblinks occurring immediately (< 100 ms) prior to the onset of the pulse.

##### General sensorimotor behavior

3.5.4.3

During the PPI and SH sessions, the smartphone’s front-facing camera and microphone passively capture a broad range of behavioral data, extending beyond the specific eyeblink responses required for the primary neurometric tests. Ten specific behaviors previously identified as differing between autistic and NA children will be analyzed in this study (22).

*Dependent variables:*

Task engagement: The percentage of trials in which the participant is not detectable within the smartphone’s camera frame.Headphone interaction: The percentage of trials with observed touching or adjustment of the headphones.Non-syllabic vocalizations: The frequency (percentage of trials) and total duration of non-linguistic vocal sounds.Postural stability: The degree of anteroposterior postural sway.Head movement: The percentage of trials with observed head rotation.Orofacial movement: The frequency and duration of mouth openings.Oculomotor activity: The mean amplitude of horizontal pupil movement per session.Vestibulo-ocular reflex (VOR) function: The correlation between the direction of head turns and compensatory pupil movement.Initial baseline variability: The variation in baseline (pre-stimulus) eyelid position during the first five trials of a session.Baseline stability: The change in the variability of baseline eyelid position from the start to the end of the session.

#### Microbiota assessment

3.5.5

For stool sample collection from children, parents will be provided with faecal collection containers and instructed to collect the sample immediately before delivery. Instructions for the parents will be provided in written format with animated graphics (Annex 11 of the **Supplementary Material**). Stool samples will be collected in an OMNIgene•GUT OM-200 (DNA Genotek Inc.; Ottawa, Canada) or a DANASTOOL (Danagen; Barcelona, Spain) tubes and transported to the laboratory facilities for their subsequent storage at -80 °C until further analysis.

The GM composition of all participants will be characterized through gene marker amplification and sequencing, which is a highly accurate and specific approach for profiling microbial communities. GM analysis will be performed as reported previously with a few modifications detailed in Annex 12 of the **Supplementary Material** (46). Briefly, this analysis will comprise four steps: DNA extraction, library preparation, sequencing and bioinformatics.

Genomic DNA (gDNA) will be extracted and purified from stool samples using a bead-beating-based approach. Library preparation will involve a PCR-amplification of the 16S rRNA V3 region, followed by the attachment of dual index barcode adapters. The indexed DNA will then be sequenced in paired-end reads of 300 bp using the Illumina MiSeq Platform. Finally, bioinformatics analysis will be performed using the DADA2 protocol (46, 47). Differences within (alpha-diversity) and between (beta-diversity) groups will be assessed using QIIME2 (48). Alpha-diversity will be quantified by Shannon diversity index, whereas beta-diversity will be evaluated using principal coordinate analysis based on Bray–Curtis dissimilarity matrices (49, 50).

#### Interviews with caregivers and health professionals

3.5.6

The perceptions of caregivers and health personnel regarding the dietary patterns and health of children and adolescents with ASD will be investigated using a qualitative approach. We will extend invitations to all parents, primary caregivers, and health professionals in the specialized education centers participating in the “Proyecto Wiñay”. Face-to-face or videocall interviews will be scheduled with interested participants, depending on their availability. Approximately 20 in-depth interviews will be conducted with caregivers and health personnel or until information saturation (i.e., repetition, absence of novelty) is reached.

The interview is thematic and semi-structured, lasting between 30 minutes and one hour. It will be recorded to ensure a verbatim transcription and coding, which will anonymize participants. The analysis will focus on key categories: challenges and opportunities for healthy nutrition in children with autism, and challenges and opportunities in caring for children’s health. A thematic analysis of the collected information will be conducted using Atlas.ti software (v 24.1.1.30813) and an inductive approach (51). The analysis process consists of six steps: familiarization with the data, creation of initial codes, searching for themes, reviewing themes, defining and naming themes, and writing the report (52). The results of the thematic analysis will also be visualized as thematic networks (53).

### Analysis plan

3.6

#### Microbiota analysis

3.6.1

Homogeneity of multivariate dispersions will be tested using the *betadisper* function in the *vegan* R package (54). Differences in microbial community composition (beta-diversity) between children with ASD and their NA peers will be determined using permutational multivariate analysis of variance (PERMANOVA) through the ADONIS2 function, also in *vegan*. Pairwise comparisons will be performed using the Wilcoxon rank sum test with Benjamini-Hochberg p-value adjustment (55).

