**Analysis:**

Group comparisons will employ multivariate regression models, adjusting for age, sex, socioeconomic status and medication use. We hypothesize significant between-group differences in dietary patterns, nutritional status, microbiota profiles, and SMD measures. Objectively measured SMD in autistic children and adolescents is expected to correlate with symptom severity, dietary patterns, and differences in microbiota composition and diversity.

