### Study limitations

4.2

This study’s primary methodological limitation is its cross-sectional design, which inherently precludes the inference of causal relationships between exposures and outcomes. Our findings will thus be restricted to identifying non-causal associations that warrant future longitudinal or experimental validation. To enhance the robustness of our findings within this observational framework, we will employ multivariate regression models to control for key potential confounders (e.g., sex, age, socioeconomic status, use of medication). We will also conduct sensitivity analyses to assess the stability of these associations under different modelling assumptions.

The generalizability (external validity) of our findings will be constrained by the recruitment strategy. Sourcing participants from specialized private healthcare centers will likely yield a sample overrepresenting families of higher socioeconomic status and better healthcare access. This strategy may also bias the cohort toward more clinically severe ASD presentations, potentially underrepresenting children with milder phenotypes or those from marginalized communities who face barriers to diagnosis.

This sampling approach was chosen to safeguard internal validity and feasibility. Centralized recruitment was essential to secure a sufficient number of professionally diagnosed participants and to administer the study’s protocols consistently. Therefore, while the results will be most directly applicable to urban-dwelling autistic children within Ecuador’s private healthcare system, they will provide high-fidelity data on the hypothesized relationships under investigation.

This trade-off is justified for the hypothesis-generating aims of this study. Following Rothman’s principles, the initial test of a mechanistic pathway (e.g., between SMD and dietary patterns) requires a well-defined cohort where exposures and outcomes can be measured with precision, even at the expense of representativeness (71). The associations identified here will provide the foundational evidence necessary to design future longitudinal and population-representative studies.

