Self-medication represents an important limitation that our study will address. In Ecuador, self-medication, particularly with antibiotics, is common across various demographic groups (75). Excluding participants based on reported medication use would severely constrain recruitment. We will therefore account for this potential confounder by adjusting for medication use in multivariable statistical models when examining associations between gut microbiota composition and other outcomes. Specifically, medication use will be included as a covariate in linear models for alpha-diversity analyses and in PERMANOVA for beta-diversity comparisons. Finally, following previously used approaches (76), we will evaluate the robustness of our findings through sensitivity analyses that leverage the detailed medication data collected, exploring drug dosage, the specific reason for medication, and the prescribing source.

Another potential limitation of our study is that no formal cognitive ability assessment will be conducted. Cognitive level can influence dietary patterns independently of sensorimotor differences, for example, by affecting a child’s ability to express food preferences or aversions. Moreover, 30–40% of children with ASD also have co-occurring intellectual disability, a rate substantially higher than among NA peers (77). To address this potential confounding, we will use CARS scores as a proxy for phenotypic severity within the ASD group. Although CARS does not measure cognitive ability directly, it correlates with functional impairment and will allow us to explore whether associations differ by severity level. Nevertheless, residual confounding by unmeasured cognitive differences cannot be entirely ruled out.

The broad age range (3–17 years) of our sample represents another limitation, given the significant developmental heterogeneity within this period. While a narrower range would reduce variability, it would also compromise sample size and generalizability. To address this, age will be included as a covariate in all multivariate models to adjust for its potential confounding effects. Additionally, we have selected age-appropriate instruments to ensure that measurements are sensitive to developmental stages. Nevertheless, residual age-related variability may still influence our findings, and we acknowledge this trade-off.

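### The pairwise microbiota follow-up is a Wilcoxon test that drops the promised covariates (and is invalid if run on distances), and two stool tubes are allowed with no stated balance or model term

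*Protocol article*

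**What the plan says.** Section 3.6.1 gives the main comparison of community composition between autistic children and their non-autistic peers to PERMANOVA. Differences "will be determined using permutational multivariate analysis of variance (PERMANOVA) through the ADONIS2 function", after a check of dispersion with betadisper. The next step is: "Pairwise comparisons will be performed using the Wilcoxon rank sum test with Benjamini-Hochberg p-value adjustment". The section names neither the outcome of that test nor the pairs, and lists no covariates.

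Adjustment is promised elsewhere. The Abstract says: "Group comparisons will employ multivariate regression models, adjusting for age, sex, socioeconomic status and medication use". Section 4.2 says that "medication use will be included as a covariate in linear models for alpha-diversity analyses and in PERMANOVA for beta-diversity comparisons", and that "age will be included as a covariate in all multivariate models to adjust for its potential confounding effects". It adds medication sensitivity analyses, "exploring drug dosage, the specific reason for medication, and the prescribing source". Section 2.3 matches Group B to Group A on sex and age.

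Section 3.5.5 has stool collected in an OMNIgene•GUT tube "or a DANASTOOL (Danagen; Barcelona, Spain) tubes and transported to the laboratory facilities". The article does not say who gets which tube, and tube type appears in none of its adjustment lists.

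**The concern.** The design has three groups, and section 4.1 presents the three-group comparison as the way to see what is specific to autism. PERMANOVA is described for autistic versus non-autistic children. The separate contrasts with typically developing children and with children who have other developmental disorders therefore seem to fall to the pairwise step, the only pairwise method stated. A rank-sum test takes no covariates, and Benjamini-Hochberg corrects only for multiplicity. Section 4.2 names self-medication, particularly with antibiotics, as a common problem that cannot be handled by exclusion. The pairwise test leaves it uncontrolled.

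Tube type is a separate matter. If the two tubes shift the measured profile differently and their use differs between groups, the shift appears as a group difference. Section 2.1 places the study in two cities over about a year. Under section 2.3, autistic children come partly from two centres and Group B from family networks. Uneven tube use is therefore possible, though it is not stated.

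**Working it through.** **Plan's own figure.** The article gives no error rate or power for the microbiota analyses. Its only sample-size figure concerns malnutrition (section 2.2.4): (1.96 + 0.84)² × (0.57×0.43 + 0.37×0.63) / 0.20² = 7.84 × 0.4782 / 0.04 = 93.7, so 94. Then 94/0.95 = 98.9, so 99, against the stated 100. It reproduces closely enough and is not in dispute. Only n = 100 per group is carried forward.

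**Step 1: what the Wilcoxon step can be run on.**

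| Outcome | Is the test valid? | Does it match the adjustment promise? |
|---|---|---|
| Shannon index | Yes, one value per child | No: it is unadjusted and sits beside the adjusted linear model of section 4.2 |
| Individual taxa | Yes, one value per child per taxon | No: it is unadjusted |
| Bray-Curtis distances | No, the inputs are dependent | No: it is unadjusted |

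No reading delivers the adjusted comparison described in the Abstract.

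**Step 2: size of the distance problem, for that reading only.** A group of 100 children gives 100 × 99 / 2 = 4,950 within-group distances, and each child enters 99 of them. The rank-sum test treats them as independent. Null simulations drew two groups of 100 from one 60-taxon logistic-normal community, with 200 runs each and nominal 5%:

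| Log-abundance SD | Within-A v within-B | Within-A v between-group |
|---|---|---|
| 1.0 | 78.5% | 66% |
| 1.0, independent repeat | 77.5% | 59% |
| 2.0 | 78.5% | 61.5% |

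**Step 3: tube type.** The documents give neither the tube split nor the size of any tube effect, so both are assumed. With tube shift d (in SD units) and tube shares q_A and q_B, the spurious group difference is d × (q_A − q_B). At 70/30 versus 30/70 this is 0.4d, or 0.12 SD at d = 0.3 and 0.32 SD at d = 0.8.

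As a normal-theory check, the standard error is √[(2/100) × (1 + d² × 0.7 × 0.3)], which is 0.143 at d = 0.3 and 0.151 at d = 0.8. The standardised biases are 0.12/0.143 = 0.84 and 0.32/0.151 = 2.1. They imply two-sided rejection of about 13% and 56 to 57%.

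Simulation of the unadjusted Wilcoxon test (4,000 runs per cell, no true group difference) agrees:

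| Tube split, A v B | d = 0.3 | d = 0.5 | d = 0.8 |
|---|---|---|---|
| 50/50 v 50/50 | 4% | 5% | 5% |
| 60/40 v 40/60 | 6% | 10% | 18% |
| 70/30 v 30/70 | 13% | 28% | 55% |
| 80/20 v 20/80 | 23% | 53% | 89% |

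With a tube term in a linear model, rejection stays between 4% and 5.5% in every cell.

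**The case against.** A reader might infer that the microbiota question as a whole is settled by unadjusted tests, so that age or medication differences pass as autism effects. The text does not support that. Section 3.6.1 gives the main composition contrast to PERMANOVA. Section 4.2 puts medication in PERMANOVA and in the alpha-diversity models, puts age in all multivariate models and adds medication sensitivity analyses. Group B is also matched on age and sex. The second aim, autistic children against non-autistic peers, can be answered from those analyses. This stands, and it limits the defect to the pairwise step.

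A reader might also take the 60 to 79% rejection rates as the error rate of the plan. They are not. The article does not say that the test is run on distances, and the within-A versus within-B version compares dispersion, which the plan assigns to betadisper. Benjamini-Hochberg over many taxa is an equally natural reading, and there the dependence among distances does not arise. This also stands.

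On the tubes, the word joining the two products does not prove that both will be used at once or unevenly. Laboratory detail is sent to Annex 12 and collection instructions to Annex 11, neither of which is shown, and the confounder list in section 4.2 is given only as examples. These points make the bias conditional. They do not remove the gap: the article fixes two alternative tubes, states several adjustment sets, and includes tube type in none of them.

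**Conclusion.** The point holds in a limited form and is worth correcting.

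- **Pairwise step.** As written, it conflicts with the plan's own promise of adjusted group comparisons whichever outcome it is applied to. If applied to Bray-Curtis distances it is also invalid, with roughly 60 to 79% null rejection at a nominal 5% under the simulated community.
- **Tube type.** The risk is conditional. It is absent if tube shares are equal across groups. It is about 13 to 55% false positives at an assumed 70/30 versus 30/70 split and 0.3 to 0.8 SD shift, and it returns to about 5% once tube type is modelled. Only if tube and group coincided completely could no analysis separate them, and nothing in the article suggests that.

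The main PERMANOVA and the alpha-diversity models are not open to the covariate criticism. Like the pairwise step, they would carry any tube imbalance unless tube type is added.

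**What to change.** In section 3.6.1, name the outcome and the pairs for the follow-up comparisons and replace the Wilcoxon step:

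- **Beta-diversity:** pairwise adonis2 with marginal tests, the same covariates as the main PERMANOVA, and Benjamini-Hochberg over the contrasts.
- **Shannon diversity and taxa:** group contrasts from covariate-adjusted models, with Benjamini-Hochberg.

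In section 3.5.5, specify one tube type for all children. If both are unavoidable, distribute them in equal proportions across Groups A, B and C within each city, record the tube for each sample, and include it as a covariate in the PERMANOVA and the alpha-diversity and taxon models. This needs to be settled before or early in collection.

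The cost is a few lines of text, slightly more analysis work and one extra data field. Choosing a single tube would also reduce purchasing flexibility.
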